#### Interim analyses {21b}

When the sample size reaches 50%, an interim analysis will be conducted by the trial steering committee, the data monitoring committee, and the study team. Analyze the risks and safety associated with the conduct of the test. Also, the accuracy of the data will be collected so far.

#### Methods for additional analyses {20b}

Currently, there is no planned additional subgroup or adjusted analyses.

#### Methods in analysis to handle protocol non-adherence and any statistical methods to handle missing data {20c}

The ITT analysis will be considered as a sensitivity check on the primary analysis with the full analysis set, and the missing data were supplemented with the last observation carried forward method.

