**Methods:**

This is a protocol paper that outlines a randomized controlled trial, patients will be assigned randomly to the PRP group, PRP+LIFU group, PRP+TENS group, and PRP+LIFU combined TENS group. The patients will be followed at 12-week and 24-week time points to evaluate the primary and secondary outcomes of the study. The primary outcome is the VAS pain score. Secondary outcomes include Western Ontario and McMaster Universities Osteoarthritis Index (WOMAC) and International Knee Documentation Committee scores (IKDC). After baseline examination, all patients will sign a written informed consent for study participation after a full explanation of the treatment protocol. We have planned a total of 120 patients (30 patients per group).

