#### Intervention description {11a}

Eligible subjects screened by inclusion and exclusion criteria will be divided into the control group, and the experimental groups by computer randomization in a random sequence with a ratio of 1:1:1:1. The control group was treated with PRP. The experimental group was treated with PRP with LIFU, PRP with TENS, and PRP with LIFU combined with TENS. Both the experimental group and the control group received PRP treatment three times, with an interval of 4 weeks. The experimental group was treated with LIFU, TENS, and LIFU combined with TENS 24 h after each PRP treatment (the injection needles healed), once a day, for five consecutive days, for a total of three courses of treatment.

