#### Outcomes {12}

Primary outcome is WOMAC score, secondary outcomes use VAS pain score, and IKDC score were performed before each PRP treatment, 3 months, and 6 months after the end of the whole course of treatment.

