#### Sample size {14}

The sample size of this study was calculated according to the uniform standard of clinical trial report and the requirement of non-inferior experiment sample content. Experimental studies have shown that the minimum clinical significance value of WOMAC scale is 12%. Based on the previous research results of our research team, we set *σ* = 28%, *β* = 0.2, power = 80%, and significance level two-tailed *α* = 0.05. In order to prevent excessive loss of subjects, the shedding rate of 10% was calculated. A total of 120 subjects (27 per group, 4 groups, 10% shedding rate) were required. ITT analysis strategy will be adopted for data analysis. Paired *T*-test analysis will be performed on the evaluation data of OA patients before and after treatment, and variance analysis will be performed on the difference analysis among multiple groups.

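### The protocol makes ITT both the analysis strategy and only a sensitivity check on an undefined full analysis set, and fixes LOCF as the sole missing-data method

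*Protocol article*

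**What the plan says.** **Analysis population.** Sample size {14}: "ITT analysis strategy will be adopted for data analysis". Methods in analysis to handle protocol non-adherence and missing data {20c}: "The ITT analysis will be considered as a sensitivity check on the primary analysis with the full analysis set". The article does not say who belongs to the full analysis set.

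**Missing data.** The same sentence in {20c} continues: "the missing data were supplemented with the last observation carried forward method". No other method is named, and it is unclear whether LOCF applies to the full analysis set, the ITT set or both.

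**Schedule.** Intervention description {11a}: all groups "received PRP treatment three times, with an interval of 4 weeks". Outcomes {12}: scores are taken "before each PRP treatment, 3 months, and 6 months after the end of the whole course of treatment". The abstract gives follow-up differently: "The patients will be followed at 12-week and 24-week time points". No section names the primary time point.

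**Expected loss.** Sample size {14}: "the shedding rate of 10% was calculated" and "A total of 120 subjects (27 per group, 4 groups, 10% shedding rate) were required".

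**The concern.** If ITT and the full analysis set were the same set, one could not serve as a sensitivity check on the other. Section {20c} therefore treats them as different and places ITT second, while {14} places ITT first. An analyst could follow either section, and could choose after seeing the data. With 30 patients per arm, leaving out a few can move the result. The blinding section {17} provides a blinded assessor but says that neither participants nor staff can be blinded, so exclusions or withdrawals related to allocation cannot be ruled out.

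LOCF assumes that a patient's score does not change after dropout, and it enters the carried value as if it had been observed. Three of the five scheduled scores are taken before or during treatment, so the carried value may describe a patient who has not yet completed the course. The arms also carry unequal burden. The three experimental arms have five daily physical-therapy sessions in each of three courses (5 × 3 = 15 treatment days), and the control arm has none. Dropout that differs by arm is therefore plausible, and it is then that LOCF distorts the comparison between groups.

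**Working it through.** **1. The plan's own figure.** The allowance for loss reproduces: 27 / (1 − 0.10) = 30 per group, and 30 × 4 = 120. The plan thus expects about 0.10 × 120 = 12 patients lost, about 3 per group. How the 27 was reached is a separate matter and is not used here.

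**2. What LOCF would carry.** Three injections 4 weeks apart put the pre-injection scores at about weeks 0, 4 and 8.
- Lost before the second score: baseline is entered at 3 and 6 months.
- Lost before the third score: week 4 is entered at 3 and 6 months.
- Lost before the 3-month visit: week 8 is entered at 3 and 6 months.
- Lost between 3 and 6 months: the 3-month score is entered at 6 months.

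If the last visit falls about 8 + 26 = 34 weeks after the first injection, a week-4 score is carried 34 − 4 = 30 weeks and a week-8 score 34 − 8 = 26 weeks. If the abstract's 24 weeks run from baseline, the gaps are 24 − 4 = 20 and 24 − 8 = 16 weeks.

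**3. Standard error for scale.** With the protocol's SD of 28 and 30 per group, the standard error of a difference between two groups is 28 × √(2/30) = 7.23. The protocol gives the SD and the threshold of 12 as percentages. They are read here as points on a 0–100 scale, which is an assumption.

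**4. Unequal dropout.** Let D be the change reached at 6 months in both arms, f the fraction of D present at the last observed score, and Δ the difference in dropout between two arms. With no true difference between the arms:

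LOCF bias = Δ × (1 − f) × D

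D, f and Δ are all assumed; the protocol gives only 10% overall loss.

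| D | f | Dropout | Bias (points) | Bias / 7.23 |
|---|---|---|---|---|
| 20 | 0.5 | 15% vs 5% | 0.10 × 0.5 × 20 = 1.0 | 0.14 |
| 30 | 0.5 | 20% vs 5% | 0.15 × 0.5 × 30 = 2.25 | 0.31 |
| 24 | 0 | 20% vs 0% | 0.20 × 1 × 24 = 4.8 | 0.66 |

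The last row is an outer case in which every lost patient carries the baseline score and all loss is in one of the two arms.

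**5. Equal dropout.** With 10% lost in each arm and a true difference of 12, LOCF gives 12 × (0.9 + 0.1f), where f is now the fraction of that difference present at dropout. The result is 10.8 at f = 0, 11.4 at f = 0.5 and 11.7 at f = 0.75.

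**6. Precision.** With 27 observed per group the standard error is 28 × √(2/27) = 7.62. Counting 3 carried values per group as observed gives 7.23, about 5% smaller (√(27/30) = 0.949), if the SD is unchanged.

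**The case against.** The case for treating this as minor has several parts.

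- **Full analysis set.** A reader might infer that it must be narrower than all randomised patients and that patients will be excluded. The article does not say so. It states no exclusion, and such a set is commonly meant to stay close to all randomised, with its definition left to a fuller document. This stands: exclusion is a possibility, not a stated plan. The conflict over which set is primary remains, because both statements are in the article.
- **Who gets an on-treatment score.** A reader might infer that all 12 expected losses would carry mid-treatment values to a 6-month primary endpoint. The documents do not support this either. Patients lost after the 3-month visit carry a post-treatment score, and neither 3 nor 6 months is named as primary.
- **Size.** The dropout differences are assumed. If all three experimental arms had the higher rate, overall loss would be (3 × 15% + 5%) / 4 = 12.5% or (3 × 20% + 5%) / 4 = 16.25%, above the planned 10%. Even so, the bias is at most about a third of a standard error in the main cases. This stands and lowers the severity.
- **Direction.** If greater burden causes more loss in the experimental arms and patients are still improving, LOCF works against those arms, which is conservative for the difference the Discussion expects. This holds under that mechanism. It would reverse if scores worsen after the last observed visit, or if the control arm loses more patients. The protocol does not settle which applies.
- **Remedy.** A baseline-adjusted mixed model would conflict with the rank tests in {20a} and with {20b}, which plans no adjusted analyses. This stands, and the fix has to cover those sections.

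**Conclusion.** The point holds at the level of should-fix. The contradiction between {14} and {20c} is on the face of the text and needs no assumption: one makes ITT the strategy, and the other subordinates it to a set that the article leaves undefined. LOCF as the only method fits this schedule poorly, because early losses place baseline or on-treatment scores at follow-up visits.

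The numerical effect of LOCF is probably modest: 1.0 to 2.25 points, or 0.14 to 0.31 of a standard error of 7.23. This rests on an assumed change of 20 to 30 points, half reached at dropout, dropout differing by 10 to 15 percentage points, and the percentage reading of the scale. It could be larger if most losses come before the second injection and fall in one arm (4.8 points in the outer case). With equal 10% dropout, a true difference of 12 would shrink to between 10.8 and 11.7. A claim that the comparison is certain to be seriously biased goes beyond what the documents show.

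**What to change.** 1. Reword {20c} so that the primary analysis includes all randomised patients in their allocated group, in agreement with {14}. Either define the full analysis set as that population or drop the term. Keep any narrower set, such as per-protocol, as sensitivity only.
2. Replace LOCF as the main method with multiple imputation or a likelihood-based repeated-measures model that uses the visits already scheduled (before the second and third injections, 3 months, 6 months).
3. Add a sensitivity analysis for data not missing at random, for example imputed values shifted to worse outcomes for patients who drop out.
4. Amend {14} (paired t-test and analysis of variance), {20a} (Wilcoxon and Kruskal–Wallis tests) and {20b} (no adjusted analyses) to match the chosen method. Multiple imputation may need less change to these sections than a baseline-adjusted model.
5. State the primary time point and whether follow-up runs from baseline or from the end of the course, so that it is clear which value is being imputed.

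The cost is revised wording in several sections, including the choice of test, and some extra analysis work. No new visits or data are needed.

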#### Plans to give access to the full protocol, participant-level data, and statistical code {31c}

Any data required to support the protocol can be supplied on reasonable request. Only de-identified datasets will be supplied.

#### Oversight and monitoring composition of the coordinating center and trial steering committee {5d}

For the credibility and validity of the trial, we set up a trial steering committee. The trial steering committee was composed of two senior professors, and the trial leader reported the progress of the trial to the steering committee every month. The steering committee was responsible for the safety of the entire trial, the avoidance of serious adverse events, the review of data at the interim analyses, and the review of patient recruitment and withdrawal. If serious adverse events occur, the trial steering committee will evaluate whether to terminate the trial.

#### Composition of the data monitoring committee, its role and reporting structure {21a}

The data monitoring committee consists of two statistical experts who are responsible for the analysis and statistics of the trial data and have no interest in the sponsor. A data audit will be held when the sample size reaches 50%.

#### Adverse event reporting and harms {22}

In our study, an adverse event will be defined as any untoward medical occurrence in a subject without regard to the possibility of a causal relationship. Adverse events will be collected after the subject has provided consent and enrolled in the study. If a subject experiences an adverse event after the informed consent document is signed (entry) but the subject has not started to receive study intervention, the event will be reported as not related to the study. All adverse events occurring after entry into the study will be recorded. An adverse event that meets the criteria for a serious adverse event (SAE) between study enrollment and hospital discharge will be reported to the local institutional review board as an SAE.

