### Objectives {7}

The objective of this study is to assess the effectiveness and safety of utilizing LIFU, TENS, and LIFU combined with TENS after patients underwent PRP for treating KOA in this randomized controlled trial. We will evaluate how well this therapy worked for patients with KOA in terms of pain and physical function. After PRP treatment, it is hoped that the physical stimulation would help patients with knee osteoarthritis experience less pain and functional improvement.

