## Methods: participants, interventions, and outcomes

### Study setting {9}

Clinicians will distribute advertising flyers and recruit patients at the outpatient clinic of West China Hospital of Sichuan University, a grade III level A hospital in southwest region of China.

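### The duty to report SAEs to the review board ends at hospital discharge, an event the protocol never describes, so the end of the reporting window is undefined

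*Protocol article*

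**What the plan says.** All places are in the protocol article.

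- **Adverse event reporting and harms {22}.** Recording is open-ended: "All adverse events occurring after entry into the study will be recorded". Reporting to the review board is not. It covers SAEs "between study enrollment and hospital discharge will be reported to the local institutional review board as an SAE".
- **Study setting {9}.** Clinicians will "recruit patients at the outpatient clinic of West China Hospital of Sichuan University". No section of the text mentions an admission, an inpatient stay or a discharge.
- **Intervention description {11a}.** Patients in all arms "received PRP treatment three times, with an interval of 4 weeks". In three of the four arms, stimulation starts 24 hours after each PRP treatment and is given "once a day, for five consecutive days, for a total of three courses of treatment".
- **Outcomes {12}.** The last assessment is 6 months after the whole course. The abstract gives follow-up at 12 and 24 weeks and states no starting point.
- **Criteria for discontinuing {11b} and the steering committee section {5d}.** The clinician reports any adverse event. The committee decides on modifying or stopping the trial and considers termination if SAEs occur. Neither section sets a time limit.
- **Post-trial care {30}.** A nurse telephones participants every 2 weeks and asks about adverse events.
- **Auditing {23}.** The review board audits the data monthly.

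**The concern.** A reporting window needs an end that staff can identify for every participant. Here the end is an event that an outpatient would not normally have. Two members of staff could read the rule differently: one stops notifying the board when the patient leaves the clinic, the other when the last course ends. An SAE between two injections, or during the months of follow-up, would then be reportable to the board or not according to who reads the rule.

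Safety is part of the stated objective, which is to "assess the effectiveness and safety of utilizing LIFU, TENS, and LIFU combined with TENS". The review board stands outside the study team, and individual SAE reports are how it learns promptly of a serious event. The section is also inconsistent within itself: recording has no stated end, while reporting to the board stops at an event that the schedule does not contain.

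**Working it through.** The plan gives no figure to reproduce. The check is arithmetic on the timeline.

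**Inputs**
- PRP on days 0, 28 and 56 (three treatments, 4 weeks apart, {11a}).
- Last stimulation session at about day 56 + 5 = 61 ({11a}).
- Last assessment 6 months after the course ({12}). At 365.25/12 = 30.44 days per month, 6 months is 182.6 days.
- Alternative: 24 weeks = 168 days (abstract), counted either from baseline or from the end of treatment.

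**Length of follow-up (last day, with first PRP as day 0)**
- A: 6 months after last PRP: 56 + 182.6 = 238.6
- B: 6 months after last stimulation: 61 + 182.6 = 243.6
- C: 24 weeks after last stimulation: 61 + 168 = 229
- D: 24 weeks from baseline: 168

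Follow-up is thus about 239 to 244 days under {12}, or 168 to 229 days under the abstract.

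**Share outside the window** = 1 − (days covered) / (last day + 1), because day 0 counts.

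| Assumed meaning of discharge | Days covered | A | B | C | D |
|---|---|---|---|---|---|
| Leaving the first visit | 1 | 99.6% | 99.6% | 99.6% | 99.4% |
| End of first course (days 0–5) | 6 | 97.5% | 97.5% | 97.4% | 96.4% |
| Each of three courses counted as a stay | 3 × 6 = 18 | 92.5% | 92.6% | 92.2% | 89.3% |
| End of all treatment (days 0–61) | 62 | 74.1% | 74.7% | 73.0% | 63.3% |

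Two cells in full: first row, schedule A, 1 − 1/239.6 = 99.6%; last row, schedule D, 1 − 62/169 = 63.3%.

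The PRP-only arm has no stimulation days, so its treatment ends on day 56 and slightly more of its follow-up falls outside. Under D this is 1 − 57/169 = 66.3%.

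**Does another section repair the rule?** Recording in {22} and the steering committee's role in {11b} and {5d} have no time limit, but neither creates a duty to report an SAE to the board. The nurse calls in {30} ask about events without saying where they are sent. The monthly audit in {23} concerns data and sets no rule for reporting individual SAEs. The answer is no.

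**The case against.** The strongest reply is that the sentence limits notification of the review board and nothing else. A reader might infer that SAEs between injections or in follow-up are missed or undercounted. The document does not support that: all adverse events after entry are recorded, no end date is set, and the nurse calls ask about them. A reader might also infer that the steering committee's power to stop the trial is weakened. That does not follow either, because the committee's information comes through {11b} and {5d}, which do not use the discharge window, and the interim review at half the sample also looks at safety. The board itself has a second route through its monthly data audit. All of this stands. What remains is narrower: no section requires an individual SAE to be reported to the board after the undefined discharge.

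A second reply is that outpatient treatment is inferred. The text states only that recruitment is at an outpatient clinic, and the design figure and timeline table are not shown. This also stands, but an inpatient stay for each course would still leave about 89% to 93% of follow-up outside.

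A third reply is that, with no discharge, the window never closes, or that discharge was meant as leaving the study. Either reading would cover everything. Nothing in the text says so, and the fix would make that meaning explicit.

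**Conclusion.** The rule fails as written. The window for reporting SAEs to the review board ends at an event that the protocol does not describe, and no other section supplies an end. If discharge is tied to a clinic visit or to the end of a treatment course, about 63% to 99.6% of follow-up falls outside the duty. The low figure needs the most generous of these meanings (end of all treatment) together with the shortest follow-up (24 weeks from baseline). Under the 6-month schedule in the Outcomes section, the most generous meaning still leaves about 74% to 75% outside.

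This rests on three assumptions: patients are treated as outpatients, which is inferred; the PRP and stimulation days follow the stated intervals; and follow-up ends as either the Outcomes section or the abstract says.

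The conclusion does not extend to loss of SAE data or to the steering committee's stopping decision. Nor does it extend to the rule that, for an event after consent but before any study intervention, "the event will be reported as not related to the study". A reader might see a causality problem there, but the rule applies only before the first intervention, which the Recruitment section places within 48 hours of initial assessment and randomization. The document gives no ground for treating it as a material fault.

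**What to change.** In Adverse event reporting and harms {22}, replace hospital discharge with the final follow-up visit as the end of the window for reporting SAEs to the review board. State the same end for recording adverse events, so that the two windows match each other and the schedule in {11a} and {12}. Since the new wording depends on when the final visit falls, reconcile the 6 months after the course in the Outcomes section with the abstract's 24 weeks at the same time.

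The two-weekly nurse calls in {30} can supply the events; a few words should say that any SAE they find goes into this reporting route.

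The cost is a short amendment for ethics approval and a few more reports. It needs no extra visits, no change to sample size and no change to the analysis.

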#### Frequency and plans for auditing trial conduct {23}

To ensure the quality of the study, the study leader will report to the trial steering committee on a monthly basis. Any discrepancies will be corrected accordingly. In addition, the IRB will conduct monthly audits of the data.

#### Plans for communicating important protocol amendments to relevant parties {25}

The study leader will be responsible for any changes to the protocol, and any changes will be submitted to the Research Ethics Committee at Sichuan University West China Hospital for approval. The study leader will disseminate the protocol changes and conduct training for all team members.

